### Recruitment

The patients will be interviewed by the blinded assessor, who will determine eligibility. Eligible patients will receive clarifications regarding the objectives of the study and will be asked to sign a statement of informed consent. Sociodemographic data and medical history will then be recorded. The assessor will collect the data related to the study outcomes at baseline, before and after a single treatment session, after the completion of the six weeks of treatment, and three months after randomization. All data will be coded and entered into Excel files (Microsoft Corporation).

### Randomization

Patients who meet the eligibility criteria will be randomly allocated to their respective intervention groups.

### Allocation concealment

The individuals will be randomly allocated to the two groups. To minimize the risk of imbalance in the size of the groups, a randomization list will be generated using two blocks: number 1 for the manipulation group and number 2 for the placebo-controlled group. The allocation sequence will be stipulated in sequentially numbered, opaque, sealed envelopes. Following the baseline evaluation, each participant will be allocated to one of the groups by opening an envelope. This process will be performed by a member of the research team who is not involved in the recruitment process or other aspects of the study.

### Blinding

The design study of the trial does not allow blinding of the therapist. All the pre- and post-treatment assessments and the follow-up assessment will be done by a person blinded to group allocation and treatment. The statistician performing the statistical analyses will also be blinded to group allocation and treatment.

### Evaluation and follow-up

The evaluation process will be conducted by a physiotherapist with experience in the evaluation procedures and blinded to the allocation of the participants to the different groups. Evaluations will be conducted in the following manner:Pre-treatment evaluationEvaluation immediately following a single intervention sessionPost-treatment evaluationEvaluation three months after randomization

### Measurements

The scales to be administered are the NPRS, ODI, EMG signal (Biering-Sorensen test and Flexion-relaxation phenomenon), FFT, and Fear-Avoidance Beliefs Questionnaire (FABQ).

### Numeric Pain Rating Scale

The NPRS will be used to determine the level of pain intensity perceived by the patient using an 11-point scale, on which 0 represents the absence of pain and 10 represents the worst pain imaginable [35]. The participants will be instructed to report their sensation of pain intensity at the moment of the evaluation to compare with the immediate effect of treatment and to report average pain intensity based on the previous seven days for comparisons at the end of the six-week treatment and three-month follow-up.

### Oswestry Disability Index

The ODI is the most commonly used outcome measure for LBP. It is a self-administered questionnaire and each section is scored on a scale from 0 (no disability) to 5 (maximum disability). The index is calculated by dividing the sum of the item scores by the maximum possible score, which is then multiplied by 100 and expressed as a percentage. Thus, for every question not answered, the denominator is reduced by 5. If a patient marks more than one statement on an item, the higher scoring statement is recorded as a true indication of disability. The questionnaire takes 3.5–5 min to complete and approximately 1 min to score [36].

### Electromyographic analysis

#### Biering-Sorensen test

Before the FRP, all individuals will perform the Sorensen endurance test [37]. The prone position will be adopted with the trunk placed beyond the edge of the table, with the anterior superior iliac spine aligned with the edge of the table and the lower limbs fixed to the table. On this test, the patient maintains the horizontal position with the upper limbs crossed and in contact with the chest for 10 s, three times, with a 10-min rest after the third time [19, 21]. The maximum 1-s root mean square (RMS) activity recorded during the Sorenson test will be defined as the maximal voluntary contraction (MVC) value and will be used as a reference for other electromyographic data.

### Flexion-relaxation phenomenon

The EMG signal will be collected during this movement. The flexion/extension trunk movement will be started in the upright position. The participant will be instructed to move in response to voice command, keeping the knees straight but not locked, and the arms hanging freely, while slowly flexing forward to full flexion over a 3-s period, pausing for 3 s at full trunk flexion and then returning to the upright starting position during the 3 s of the trunk extension period. This protocol is typical of those used in studies on the FRP [17, 18, 21, 27].

The movement will be performed three times. Data from the third replication will be used in the analysis. Before the first reading, the patients will practice three times to become familiar with the movement [20, 21].

Two different forms of a flexion-relaxation ratio (FRR) will be used to quantify the degree to which the FRP is present [17, 18]. One will be calculated by dividing the maximum RMS of EMG activity level during flexion (while bending forward) by the lowest mean EMG activity as measured over a 1- interval during the fully flexed phase. Another FRR will be similarly calculated by dividing the maximum RMS EMG activity level during extension (while returning to the upright position) by the same minimum. The beginning and end of the fully flexed phase for each cycle will be determined from the plot of the motion data.

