Individuals with chronic LBP do not reach the flexion-relaxation phenomenon (FRP), which is the decrease in or absence of electromyographic activity in the paraspinal muscles found during full trunk flexion in asymptomatic individuals [17–19]. In patients with LBP, the absence of this phenomenon may be due to muscle spasms, decreased range of motion, exaggerated stretch reflexes, or the protection of injured passive structures [26].

Based on the literature, there are indications that the FRP may be a valuable clinical tool to assist in the diagnosis and treatment of patients with LBP [17, 18, 24, 27] and there have been very few studies on the use of visceral techniques for such patients. Thus, the aim of the proposed study is to determine whether osteopathic visceral manipulation (OVM) can modulate stabilizing neuromuscular responses of the lumbar spine and reduce both pain intensity and disability in individuals with non-specific chronic LBP and functional intestinal constipation.

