### Outcome measures

A blinded assessor will record outcome measures.

The primary outcomes will be LBP intensity (NPRS) and the Oswestry Disability Index (ODI) after the six weeks of treatment and three months after randomization, because pain is the most common reason patients seek private physical therapy clinics for the treatment of LBP. From a patient’s perspective, it is also the outcome that most determines whether treatment has been successful [32].

The secondary outcomes will be the EMG signals during the FRP and fingertip-to-floor test (FFT) after the first treatment session, after the six weeks of treatment and three months after randomization and the FABQ after the six weeks of treatment and three months after randomization.

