### Statistical analysis

Statistical analysis will be performed using intention-to-treat analysis. If data losses occur during the study, the last observation will be carried forward to adjust the missing data in follow-up evaluations. The Shapiro–Wilk test will be used to determine the normality of the data. Anthropometric differences between groups will be determined using the independent t-test for data will normal distribution and the Mann–Whiney test for data with non-normal distribution. Repeated-measures analysis of variance (ANOVA) followed by the Bonferroni post hoc test will be used to determine the effects of treatment with regard to the NPRS, RMDQ, FFT, FABQ, and EMG considering the following interactions: group (OVM and SOVM) vs evaluation (pre-interventions, after one session, after six weeks, and three months after randomization) vs movement (flexion extension). If the data exhibit non-normal distribution, Friedman’s ANOVA will be used with Dunn’s post hoc test. A *p* value < 0.05 will be considered indicative of statistical significance. The data will be organized and tabulated using the Statistical Package for the Social Sciences (SPSS, v.19.0).

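### The flexion-relaxation ratios are likely to be right-skewed, and the plan's only remedy for non-normal data is Friedman's test, which has no group factor

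*Protocol article*

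**What the plan says.** In the protocol article, the section Flexion-relaxation phenomenon defines two ratios. The first divides the peak RMS during forward bending "by the lowest mean EMG activity as measured over a 1- interval during the fully flexed phase". The second is obtained "by dividing the maximum RMS EMG activity level during extension (while returning to the upright position) by the same minimum". Nothing is averaged over repetitions: "Data from the third replication will be used in the analysis".

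The Background describes the phenomenon as a "decrease in or absence of electromyographic activity in the paraspinal muscles found during full trunk flexion". It attaches that description to asymptomatic people and says of the trial's population: "Individuals with chronic LBP do not reach the flexion-relaxation phenomenon (FRP").

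Under Outcome measures the EMG result is secondary: "The secondary outcomes will be the EMG signals during the FRP and fingertip-to-floor test (FFT").

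The Statistical analysis section lists EMG with the other outcomes and gives one rule for all of them. Normality is checked by Shapiro–Wilk and the default is repeated-measures ANOVA with Bonferroni comparisons. "If the data exhibit non-normal distribution", the analysis becomes Friedman's ANOVA with Dunn's comparisons. No transformation is named, and none is ruled out.

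**The concern.** A ratio whose denominator becomes small in the patients who do best has a long right tail. The better the flexed-phase relaxation, the larger and less stable the FRR. With only the third repetition used, a small minimum is not averaged out.

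The protocol's rule for such data leads to a test that cannot answer the trial's question. Friedman's test ranks each patient's evaluations against one another. It can say whether values change over time within a set of patients, but it has no term for OVM versus sham. Running it separately in each arm and comparing the two p-values is not a between-group test either.

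At stake is the trial's mechanistic result. It is formally secondary, although the Abstract and the Discussion both present the effect on flexion-relaxation as what the study sets out to show.

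**Working it through.** **1. The plan's own figures.** There is no mean, SD or CV for either FRR, so no stated FRR figure can be reproduced. The only computed figure is the sample size. The standardised difference is 10/12 = 2.5/3.0 = 0.833, and 32 per group gives t-test power 0.907 at two-sided 0.05, in line with the stated 90%. That calculation concerns ODI and NPRS only. The check below uses the planned 38 per arm; every CV in it is an assumption.

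**2. Shape of the ratio.** Write FRR = P/m, with P the peak and m the flexed-phase minimum. If m falls to 20% of its usual level with P unchanged, FRR is multiplied by 1/0.2 = 5. For log-normal parts,

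log-SD = √[ln(1 + CV_P²) + ln(1 + CV_m²)].

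With CV_P = 0.3 and CV_m = 0.5 this is √(0.086 + 0.223) = 0.56. The CV of the ratio is √(exp(log-SD²) − 1), so log-SD 0.6 corresponds to 66% and log-SD 1.2 to 180%.

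**3. How often Shapiro–Wilk rejects at 5%** (simulation, one sample of 38):

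| Assumed model | Setting | Rejection |
|---|---|---|
| Normal parts, CV_P 0.3 | CV_m 0.1 / 0.2 / 0.3 / 0.4 | 8% / 36% / 81% / 97% |
| Log-normal parts, CV_P 0.3 | CV_m 0.1 / 0.2 / 0.3 / 0.5 / 0.75 / 1.0 | 47% / 59% / 70% / 89% / 98% / about 100% |
| Log-normal ratio | ratio CV 66% | 92% |
| Mixture: some patients relax to 20% of the usual minimum | 0% / 5% / 10% relax | 42% / 92% / 99% |

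On the log scale, log-normal ratios are rejected in about 5–6% of samples at every CV tried.

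The level at which the check is applied also matters. Suppose it is run in each of the 2 arms × 4 evaluations = 8 cells, with an assumed within-patient correlation of 0.6. At least one cell then fails in 98% of trials at a ratio CV of 31%, and in about 32% even when the data are exactly normal.

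**4. If the check fails.** The Friedman route is rank-based, so extreme values do not dominate it. What is lost is the group comparison itself.

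**5. If the raw-scale ANOVA is kept.** As a stand-in, take a two-sample t-test at one evaluation, 38 per arm, with a shift of 0.65 log-SD. The noncentrality is 0.65 × √(38/2) = 2.83, which gives about 80% power on the log scale.

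| log-SD | 0.31 | 0.35 | 0.56 | 0.6 | 0.73 | 0.8 | 0.88 | 1.0 | 1.2 |
|---|---|---|---|---|---|---|---|---|---|
| Raw-scale power | 78% | 77% | 74% | 73% | 71% | 68% | 65% | 61% | 54% |

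Raw-scale type I error stayed between 4.4% and 5.2% for denominator CVs from 0.1 to 1.0.

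Extreme values do carry weight on this route. The two most extreme of 38 values supply 27% of the sum of squares for normal data, 33–54% for log-normal ratios with CV_m 0.1–1.0, and 72% if 5% of patients relax.

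**6. The shared denominator.** On the log scale, log(F/m) − log(E/m) = log(F/E): the flexion-versus-extension contrast no longer contains m. On the raw scale, F/m − E/m = (F − E)/m, and m stays in.

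**The case against.** The strongest reply is that the article is a condensed document, that it excludes no transformation, and that a log scale for a secondary ratio is ordinary SAP content. This is right as far as silence goes: a reader might infer that the plan commits to untransformed ratios, and it does not say so. But the article is not silent on what to do with non-normal data. It fixes Friedman's test, and that stated instruction is what fails.

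Second, a reader might infer that denominators will be near zero throughout. The Background ties absent activity to asymptomatic people and says that chronic low back pain patients do not reach the phenomenon. Near-zero minima are therefore a matter of responders after treatment, and the documents do not say how many to expect.

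Third, with little variation in the minimum and a single pooled check, failure may be as rare as 8%. This stands: certain failure of the normality check is not supported.

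Fourth, the missing group factor is not peculiar to the FRR. It affects every outcome listed in the Statistical analysis section, the primary NPRS included. That is true. The FRR is singled out because its construction makes skew likely, and because a log scale is a natural remedy for it.

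Finally, one might read the planned group-by-evaluation-by-movement interaction as a test that is blind to relaxation. The documents do not support calling that an error. The cancellation occurs only after logging, the section does not name that interaction as the test of the phenomenon, and it is an inference that movement there indexes the two ratios. It is a caution for the log-scale analysis.

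**Conclusion.** The point holds in a limited form. Both ratios share a denominator that shrinks with relaxation, right skew is likely, and the stated remedy for non-normality removes the OVM versus sham comparison for this outcome.

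The probability of taking that route cannot be fixed from the documents; under the assumed CVs it runs from about 8% to near 100%. The alternative route costs power, about 54–78% where the log scale has 80%, and does not inflate type I error. These are alternative harms, not cumulative ones: a trial that goes to Friedman does not also suffer the raw-scale loss. The power figures come from a single-evaluation t-test with log-normal data and no dropout, so they indicate size only.

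The primary outcomes' sample size of 76 is unaffected. The point is worth correcting because the correction is almost free.

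**What to change.** State that each FRR is analysed as log(FRR) in a repeated-measures model with group, evaluation and group-by-evaluation terms. Report the between-group difference in change at each evaluation as a ratio of geometric means with a 95% CI.

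Read the treatment effect from the group-by-evaluation term within each ratio, not from the flexion-versus-extension contrast, which cancels the shared denominator on this scale.

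Remove the Friedman fallback for these outcomes. The same fallback needs attention wherever else that section applies it.

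The cost is a change of analysis wording, with no new data or patients. The one downside is that effects are expressed as ratios of geometric means. Logging adds no new difficulty with a zero minimum, since the ratio itself is undefined there.

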### Electromyographic signal

Electromyography is the most widely used assessment tool for the study of muscle activation during the FRP [17, 18]. A four-channel conditioning module (BTS FREEEMG 1000®) will be used with an A/D converter with 16-bit resolution, a common rejection mode ratio > 100 dB and 20–450 Hz bandpass filter. The EMG signals will be amplified with a 2000-fold gain using a 1-kHz sampling frequency and wireless transmission. The signals will be captured with self-adhesive, disposable, Ag/AgCl surface electrodes measuring 1 cm in diameter (Medi-Trace 200 Kendall Healthcare, Tyco, Canada). After cleaning the skin of the sites with 70% alcohol, the electrodes will be positioned at a distance of 2 cm center to center on the paraspinal muscles at T12 and L1 on each side with approximately 1 cm vertical distance between the edges of the electrodes in semi-flexed trunk position [21, 27]. The electrodes will not be removed during treatment, but the outline of each electrode will be made with a skin marking pen so that they can be placed in the same location for subsequent measurements if they become detached during treatment.

### Fingertip-to-floor test

The FFT will be performed during the third cycle of the FRP with full trunk flexion (static phase). The third finger of the dominant hand will be used [38]. The participants will stand on a platform measuring 30 cm in height to avoid touching the floor, which would make the measurement unviable.

### Fear-Avoidance Beliefs Questionnaire

The FABQ is a 16-item instrument used to determine a patient’s beliefs regarding the effects of physical activity and work on musculoskeletal pain. The responses for each item are scored on a seven-point scale (0 = completely disagree to 6 = completely agree). The original factor analysis revealed two subscales: a physical activity subscale with five items (maximum score = 24) and the work subscale with 11 items (maximum score = 42). The total is in the range of 0–96 points, with a higher score indicating more strongly held fear-avoidance beliefs. The FABQ takes about 10 min to complete [39].

### Statistical analysis

Statistical analysis will be performed using intention-to-treat analysis. If data losses occur during the study, the last observation will be carried forward to adjust the missing data in follow-up evaluations. The Shapiro–Wilk test will be used to determine the normality of the data. Anthropometric differences between groups will be determined using the independent t-test for data will normal distribution and the Mann–Whiney test for data with non-normal distribution. Repeated-measures analysis of variance (ANOVA) followed by the Bonferroni post hoc test will be used to determine the effects of treatment with regard to the NPRS, RMDQ, FFT, FABQ, and EMG considering the following interactions: group (OVM and SOVM) vs evaluation (pre-interventions, after one session, after six weeks, and three months after randomization) vs movement (flexion extension). If the data exhibit non-normal distribution, Friedman’s ANOVA will be used with Dunn’s post hoc test. A *p* value < 0.05 will be considered indicative of statistical significance. The data will be organized and tabulated using the Statistical Package for the Social Sciences (SPSS, v.19.0).

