### Sample size calculation

The sample size was calculated using G Power 3.1.9.2 software. This calculation was based on the detection of a 10-point difference on the ODI and 2.5-point difference on the NPRS, which have been identified as the minimum clinically important differences [33]. A sample size of 32 participants per group would provide a 90% power to detect a clinically important difference between groups, assuming a common standard deviation of 12 on the ODI [34] and 3.0 on the NPRS and a two-sided hypothesis with an alpha level of 0.5. The sample will be increased by 20% to compensate for possible dropouts, leading to 38 individuals in each group (overall sample = 76 participants).

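### Last observation carried forward is the only stated missing-data rule for the primary NPRS and ODI outcomes; it can bias the group difference and can let momentary pain stand in for a seven-day average

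*Protocol article*

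**What the plan says.** The Statistical analysis section of the protocol article states "Statistical analysis will be performed using intention-to-treat analysis" and then gives one rule for lost data: "the last observation will be carried forward to adjust the missing data in follow-up evaluations". It names no exception, alternative or sensitivity analysis.

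The Outcome measures section makes NPRS and ODI primary, each at six weeks and at three months after randomization. The repeated-measures ANOVA uses one evaluation factor for all outcomes, "evaluation (pre-interventions, after one session, after six weeks, and three months after randomization". The only evaluations before six weeks are therefore pre-treatment and immediately after one session.

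The Numeric Pain Rating Scale section defines two recall periods. Around the single session, participants report "pain intensity at the moment of the evaluation to compare with the immediate effect of treatment". For the later visits they report "average pain intensity based on the previous seven days for comparisons at the end of the six-week treatment and three-month follow-up".

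The plan expects losses. Under Sample size calculation: "The sample will be increased by 20% to compensate for possible dropouts".

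**The concern.** Carrying a value forward assumes that the score would not have changed after the patient was lost, in a trial built to detect change. The filled value is then analysed as if it had been measured.

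Three substitutions follow from the wording, with differing certainty:

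- **Lost after six weeks:** the end-of-treatment score becomes the three-month score. Durability is assumed for these patients, not measured.
- **Lost before six weeks, if the rule applies at that visit:** the entry is the baseline or a value taken after session 1, before five of the six sessions.
- **NPRS in that second case:** the ANOVA puts the post-session-1 evaluation in the same series as the later ones. The carried value can then be pain at one moment, just after treatment, standing in for a weekly average. That is a different measurement.

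At stake is the estimated group difference on both primary outcomes.

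**Working it through.** **1. The plan's own figures.** Inputs from Sample size calculation: differences of 10 (ODI) and 2.5 (NPRS), SDs of 12 and 3.0, 90% power, two-sided. Both outcomes give a standardised difference of 10/12 = 2.5/3.0 = 0.833. A two-sample t-test at alpha 0.05 needs 31.25, so 32 per group, with power 0.907. The stated 32 is reproduced. (That section prints alpha as 0.5, whereas Statistical analysis uses 0.05; this is a separate matter.) Inflation: 32 × 1.2 = 38.4, stated as 38. The loss this absorbs is (38 − 32)/38 = 6/38 = 15.8%. A loss of 20% would leave 38 × 0.8 = 30.4.

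**2. Expected estimate under carry-forward.** Let dO and dS be the loss in the OVM and sham arms, c the sham improvement, Δ the true difference, and a and b the improvements carried in OVM and sham (0 if baseline is carried). With loss unrelated to outcome within each arm:

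estimate = [(1 − dO)(c + Δ) + dO·a] − [(1 − dS)c + dS·b]

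Positive values favour OVM. All values of dO, dS, c, a and b below are assumptions.

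- **Equal loss d, baseline carried:** estimate = (1 − d)Δ. At d = 0.158: NPRS 2.5 × 0.842 = 2.1; ODI 10 × 0.842 = 8.4. At d = 0.20: 2.0 and 8.0.
- **No true effect, equal loss, baseline carried:** (1 − d)c − (1 − d)c = 0. No bias.
- **No true effect, loss 10% OVM and 30% sham, baseline carried:** NPRS with c = 2: 0.9 × 2 − 0.7 × 2 = 0.4. ODI with c = 10: 9 − 7 = 2. Reversing the split reverses the sign.
- **True effect, loss 30% OVM and 10% sham, baseline carried:** ODI 7.0 (c = 0) to 5.0 (c = 10); NPRS 1.75 (c = 0) to 1.35 (c = 2). With 10% OVM and 30% sham: ODI 9.0 to 11.0; NPRS 2.25 to 2.65.
- **Momentary NPRS carried:** 20% loss per arm, no lasting difference (1-point improvement in both arms), immediate improvement 3 in OVM and 0 in sham: (0.8 × 1 + 0.2 × 3) − (0.8 × 1 + 0.2 × 0) = 0.6 points in favour of OVM.

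**3. Loss after six weeks.** With equal loss d between the two visits, the three-month estimate is (1 − d)Δ3 + dΔ6, where Δ3 and Δ6 are the true differences at three months and six weeks. As an extreme case, take Δ6 at the design value, Δ3 = 0 and all of the 6/38 lost late: 2.5 × 6/38 = 0.39 NPRS points and 10 × 6/38 = 1.6 ODI points remain although the effect has gone.

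**4. Simulation.** 20,000 trials, 38 per arm, baseline–outcome correlation 0.5 (assumed), loss completely at random within arm, baseline carried, t-test on the final value (simpler than the planned ANOVA), lost patients rounded to whole numbers.

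| Scenario | Carry-forward | Observed cases |
|---|---|---|
| Design effect, 20% loss per arm: power | 0.72–0.80 | about 0.89 |
| Design effect, 30% OVM / 10% sham: power | 0.35–0.70 | about 0.89 |
| No effect, 10% / 30% either way, both arms improving by ODI 10 or NPRS 2: type I error | 0.08 (ODI), 0.07 (NPRS) | about 0.05 |
| No effect, 20% per arm, same improvement: type I error | 0.04–0.05 | about 0.05 |

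**The case against.** Several points on the other side stand and limit the claim.

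- **Momentary pain is not certain to be carried.** A seven-day comparison implies a seven-day baseline. If current pain and seven-day pain are kept as two variables, the rule carries the seven-day baseline. A reader might infer that every early dropout will have momentary pain entered; the text allows this but does not settle it.
- **The reach of the rule is uncertain.** In the Abstract and in the Blinding and NPRS sections, follow-up refers to the three-month visit. The plural in Statistical analysis favours the wider reading. On the narrow one, only the six-week to three-month carry remains, and the article states no rule for missing six-week data.
- **The ODI value carried may not be baseline.** Outcome measures lists no ODI after session 1, but Recruitment and the ANOVA's evaluation factor do not exclude one.
- **The 20% is not a forecast for each arm at six weeks.** The inflation absorbs 15.8%, and this covers loss at any time.
- **Unequal dropout is assumed.** The sham is matched in contact points, duration and sessions, and patients are blinded. With SD 3.0 and 38 per arm the standard error is 3.0 × √(2/38) = 0.69, so a spurious 0.4 is about 0.6 standard errors.
- **The bias has no fixed direction.** A reader might infer that the rule favours OVM. With equal loss, baseline carried and a real effect, it weakens the estimate. A reader might also infer that it always inflates false positives; in the simulations with no effect and equal loss, it did not.

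None of this supports the rule. Its validity needs scores that stay still after dropout, and the protocol gives no ground for that. Nor is this a detail left to an unseen analysis plan: the method is stated.

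**Conclusion.** The concern holds in this form: carry-forward is the sole stated rule for missing follow-up data on both primary outcomes, and it can bias the group difference. The three-month carry follows from the text on either reading of follow-up. The six-week carry rests on the wider reading, and the use of momentary pain rests on NPRS being treated as one series.

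The size cannot be fixed from the document, because dropout by arm and sham improvement are not given. Under the stated assumptions it runs from no bias (no effect, equal loss, baseline carried), through a 16% to 20% loss of a true effect (equal loss), to a spurious 0.4 NPRS points (10% against 30% loss, both arms improving by 2). No corrected sample size follows from this point.

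**What to change.** Replace carry-forward with a likelihood-based mixed model for repeated measures on the seven-day NPRS and on the ODI. Enter baseline, six weeks and three months as outcome occasions, and constrain the baseline mean to be equal across arms. Every randomised patient with a baseline then contributes in the assigned arm. Baseline as a covariate only would not achieve this: patients with neither a six-week nor a three-month value would drop out of the model, and these are the early losses at issue. Multiple imputation under missing at random is an equivalent option.

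The text should also:

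- state the recall period of the baseline NPRS;
- analyse momentary NPRS separately, as the immediate effect, and never carry it into the seven-day endpoint;
- add one missing-not-at-random sensitivity analysis, with a delta shift over a range stated in advance.

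The cost is revised analysis text, a little more analysis work and slightly wider confidence intervals. Visits, sample size and interventions do not change. The change should be made before unblinding.

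### The four-visit ANOVA of the NPRS primary mixes momentary with seven-day pain and lets a transient difference after session one decide the group-by-evaluation test

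*Protocol article*

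**What the plan says.** The Statistical analysis section prescribes one repeated-measures ANOVA with Bonferroni post hoc tests "with regard to the NPRS, RMDQ, FFT, FABQ, and EMG considering the following interactions". The factors are group (two arms) and "evaluation (pre-interventions, after one session, after six weeks, and three months after randomization) vs movement (flexion extension". The section does not say that any factor or visit applies to some outcomes only. Missing follow-up data are filled by carrying the last observation forward.

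Outcome measures names the primary outcomes and their time points as "LBP intensity (NPRS) and the Oswestry Disability Index (ODI) after the six weeks of treatment and three months after randomization". The visit after the first session is listed there for "EMG signals during the FRP and fingertip-to-floor test (FFT) after the first treatment session", not for pain, disability or fear-avoidance beliefs.

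The Numeric Pain Rating Scale section uses two recall periods. For the first comparison, around a single session, patients are asked to "report their sensation of pain intensity at the moment of the evaluation to compare with the immediate effect of treatment". The later ratings instead rest on a different recall, namely "average pain intensity based on the previous seven days for comparisons at the end of the six-week treatment and three-month follow-up". It does not say explicitly which recall the baseline rating uses.

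**The concern.** For pain, the four levels of the evaluation factor are not the same measurement. The rating after session one is pain at that moment; the ratings at six weeks and three months are weekly averages. Whichever recall the baseline uses, a single four-level factor combines both.

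Three things are at stake.

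- The time effect and the within-arm visit-to-visit comparisons partly reflect the change of question.
- For a patient lost after session one, the last NPRS on file may be momentary, and nothing in the text stops it from filling the six-week or three-month seven-day slot.
- The group-by-evaluation test has three degrees of freedom and includes a visit that is not a primary time point for pain. A short-lived response to the first session can make it significant and be read as an effect of the six-week programme, which is what the primary objective asks about.

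**Working it through.** **Sections side by side**

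| Outcome | Visits in Outcome measures, plus baseline | Recall or movement |
|---|---|---|
| NPRS | 6 weeks, 3 months | momentary for the immediate effect; seven-day later |
| ODI | 6 weeks, 3 months | no movement level |
| FABQ | 6 weeks, 3 months | no movement level |
| FFT | after session one, 6 weeks, 3 months | single reading in full flexion |
| EMG | after session one, 6 weeks, 3 months | flexion and extension ratios |

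For the NPRS, a fourth level is reached only by adding the momentary rating.

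**The plan's own figure.** The Sample size calculation section gives a difference of 2.5 and an SD of 3.0 for the NPRS, so d = 2.5/3.0 = 0.833 (the ODI gives 10/12 = 0.833). By the noncentral t distribution at two-sided 0.05, power is 0.898 with 31 per group and 0.907 with 32. The stated 32 per group at 90% power is reproduced. That section prints alpha as 0.5; I use the 0.05 of the Statistical analysis section.

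**Inputs for the check.** n = 32 per arm and SD σ = 3.0 (Sample size calculation). The within-patient correlation ρ is not given in the protocol; I assume 0.5, equal for all pairs of visits, and show 0.3 and 0.7.

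**Interaction test.** Let δ be the vector of group differences across k visits. The noncentrality is λ = (n/2) × Σ(δ − mean δ)² / [σ²(1 − ρ)], referred to F with k − 1 and (k − 1)(2n − 2) degrees of freedom.

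*Difference c after session one only, four visits.* δ = (0, c, 0, 0), so the sum is 0.75c². At ρ = 0.5, λ = 16 × 0.75c² / 4.5 = 2.667c², on 3 and 186 df.

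| c (points) | λ at ρ = 0.5 | Significant, ρ = 0.5 | ρ = 0.3 | ρ = 0.7 |
|---|---|---|---|---|
| 1.0 | 2.67 | 24% | 18% | 39% |
| 1.5 | 6.00 | 51% | 37% | 75% |
| 2.0 | 10.67 | 78% | 62% | 95% |
| 2.5 | 16.67 | 94% | 83% | >99% |

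*The same truth over baseline, six weeks and three months.* δ = (0, 0, 0), λ = 0, so the rate is the nominal 5%.

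*Recall offset c shared by both arms.* It cancels from δ, so the interaction stays at 5%; simulation gave 5.2% to 5.8%. The time effect does move. With baseline and post-session ratings momentary and the later ones seven-day, λ = 2n × c² / [σ²(1 − ρ)] = 64c²/4.5 = 14.22c². Offsets of 0.5, 1.0 and 1.5 points make it significant in 32%, 89% and more than 99% of trials with no true change.

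*Price of dropping the visit.* For a 2.5-point effect present at six weeks and three months but not after session one, four visits give a sum of 6.25, λ = 16 × 6.25/4.5 = 22.2 and power 98%. Three visits give a sum of 6.25 × 2/3 = 4.17, λ = 14.8 on 2 and 124 df, and power 94%. If the effect is already present after session one, four visits give λ = 16.67 and power 94%, so nothing is lost.

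**The case against.** The Numeric Pain Rating Scale section already separates the recalls by purpose, and it can be read as two comparisons, each with its own baseline. Both arms answer the same question at each visit, so the randomised comparison is protected from a common recall offset. An early effect can feed an omnibus interaction in any four-visit model, whatever the recall, and the Bonferroni tests could show where it arose. Much of this stands. It does not remove the conflict: the Statistical analysis section does not repeat the separation, places all four evaluations in one factor, and does not say which contrast decides the pain outcome.

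Stronger readings are tempting but not supported.

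- A reader might infer that the model cannot be run for most outcomes, because only EMG has flexion and extension values. An analyst would simply drop that factor elsewhere; this is compressed wording and biases nothing.
- A reader might infer that no ODI or FABQ data exist after session one. Outcome measures lists "the FABQ after the six weeks of treatment and three months after randomization" and treats the ODI likewise, but Recruitment and Evaluation and follow-up give four evaluations without splitting them by outcome, and the schedule figure is not shown. Absence of data is an inference. For the same reason, it is speculation that carry-forward would fill an unscheduled visit.
- A reader might say the two pain ratings are on different scales. Both use the same 0 to 10 scale; only the recall period differs.

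**Conclusion.** The point holds for the NPRS primary and should be settled before any data are analysed. As written, the omnibus test can be significant because of a transient difference at a visit that is not a primary time point for pain: about 24% to 94% of trials for differences of 1.0 to 2.5 points, against 5% without that visit. Such a rejection is not a false positive in the strict sense, since a difference exists at one visit; it is an answer to a different question from the primary objective. The figures rest on 32 per arm, SD 3.0, an assumed equal correlation of 0.5, and no group difference at the other visits.

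It would be wrong to conclude that mixing the recalls by itself inflates the group-by-evaluation test. A shared offset leaves it near 5% and distorts only the time effect and the within-arm comparisons. Between-group contrasts at six weeks and three months are sound if the baseline uses seven-day recall and no momentary score is carried into those visits.

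**What to change.** - Analyse the NPRS (seven-day average, with a seven-day baseline) and the disability primary over baseline, six weeks and three months only, with group contrasts at six weeks and three months.
- Analyse momentary NPRS before versus after session one separately, as secondary.
- State that a momentary score is never carried forward into a seven-day slot.
- As accompanying clarification, restrict the movement factor to EMG, and give FABQ and the disability index only the visits set in Outcome measures. The analysis sentence names the RMDQ where the stated primary is the ODI; that is a separate point, but the same rewrite should settle it.

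This is mainly a change of wording, since both recall versions are already planned; the one addition is to state that the baseline includes a seven-day rating. The omnibus test may lose a little power, about 94% against 98% for a 2.5-point effect that appears after the first session and is sustained, and none if the effect is already present after that session.
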